### Recruitment

Patient recruitment will be conducted among inpatients at each center; patients who meet the inclusion criteria will be informed of the study and receive relevant information. Potential patients will be further examined by the researcher (doctor), and eligible patients will be identified after medical history collection and ultrasound examination. Each participating patient will be informed about the trial process, treatment methods, risks, compensation, and follow-up. Finally, the patient or their guardian will provide informed consent.

### Statistical analysis

Analysis will follow the intention-to-treat (ITT) and per-protocol (PP) principles. Continuous outcomes (AVVQ score, VCSS, VAS score, and CIVIQ) will be analyzed using linear mixed models (LMMs) adjusted for baseline values, center, CEAP class, and time. Non-inferiority will be declared for the AVVQ score at 12 months if the upper limit of the 95% CI for the difference (OM-SM or TM-SM) is <*δ* (2.0 points). Recurrence rates will be compared using Kaplan-Meier survival analysis and Cox proportional hazards models. Complications will be compared using chi-square tests or Fisher’s exact tests. Compliance will be summarized descriptively. Subgroup analyses (e.g., by CEAP class, ablation type) are planned. Sensitivity analyses will be performed to assess the impact of missing data. SPSS version 21.0 will be used. *p* < 0.05 will be considered to indicate significance for superiority analyses.

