### Sample size and study duration

According to previous studies (27–32) and recent systematic analyses, the 12 month recurrence rate after the thermal ablation of VVs in the lower extremities is approximately 3%–5%. The setting in the OM group is 4% and the non-inferiority threshold *δ* is −6% (17). With a statistical power of 90% and a significant equivalence of 1.7% (one-sided), at least 511 patients (170 in each group) needed to be recruited. However, considering the potential withdrawal rate of 20% and the very low incidence of adverse events in this trial, the total sample size was increased to 600 patients (200 in each group). The patients will be followed up for 12 months, and the study is expected to last for 36 months.

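### The trial is sized for non-inferiority at one-sided 1.7%, but the analysis never uses that level: its only non-inferiority rule reads a 95% CI (one-sided 2.5%), on a secondary outcome

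*Protocol article*

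**What the plan says.** - **Sizing** (Protocol article, Sample size and study duration). The calculation is for recurrence at 12 months, which the Primary outcome section names as primary. It assumes 4% in the OM group, a margin of 6 percentage points (written with a minus sign), 90% power and "a significant equivalence of 1.7% (one-sided"). The result is 511 patients, 170 per group, raised to 600. The origin of 1.7% is not explained.
- **Non-inferiority rule** (Statistical analysis). The one rule given is for AVVQ at 12 months, with a margin of 2.0 points. It applies "if the upper limit of the 95% CI for the difference (OM-SM or TM-SM") is below that margin.
- **Recurrence** (Statistical analysis). Kaplan-Meier and Cox models are named. No margin, confidence level or non-inferiority criterion is attached to them.
- **Superiority** (Statistical analysis). A p-value below 0.05 "will be considered to indicate significance for superiority analyses".
- Neither section states a family-wise level, a multiplicity adjustment or a testing order.

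**The concern.** A non-inferiority trial rests on one chain: endpoint, margin, error level, and the interval from which the decision is read. Here the chain breaks between two sections. The level used for sizing is not the level used for deciding, and the endpoint that was sized has no decision rule at all.

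The figure 1.7% is close to 5%/3 = 1.67%. That suggests a three-way Bonferroni share for three arms, although the protocol does not say so. If that was the intention, it has not been carried into the analysis.

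What is at stake is the threshold itself. A shorter regimen could be non-inferior on a 95% interval and fail on the 96.6% interval that matches the sizing. With two levels in the document and no stated family, a reader cannot tell which error rate a positive result carries, and the choice could be made after the data are seen.

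**Working it through.** **Inputs.** From the protocol: recurrence 4%, margin 6 points, one-sided 1.7%, power 90%, 170 and 200 per group, a 95% CI for two comparisons. Assumed: the same 4% in the other arms (only OM is stated), a two-sided 95% CI, and equal arms, so that OM-SM and TM-SM have correlation 0.5 through the shared SM arm.

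**1. The plan's own sample size.** n per arm = (z₁₋α + z₁₋β)² × 2p(1−p)/δ².
- At 1.7%: (2.120 + 1.282)² × 2(0.04)(0.96)/0.06² = 246.8, so 247 per arm (741 in total). The stated 170 per arm (511) is not reproduced.
- At 2.5%: (1.960 + 1.282)² × 21.33 = 224.2, so 225 per arm (675 in total).

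That shortfall is a separate matter. It is relevant here because changing the level does not by itself restore 90% power.

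**2. The two levels on one scale.**
- A two-sided 95% CI is a one-sided 2.5% test, z = 1.960.
- One-sided 1.7% corresponds to a two-sided interval of 1 − 2 × 0.017 = 96.6%, z = 2.120.
- Ratio of error levels: 2.5/1.7 = 1.47. Ratio of interval widths: 2.120/1.960 = 1.08.

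**3. At least one false claim, OM-SM or TM-SM, both at the margin.** This is 1 − P(Z₁ < z, Z₂ < z) for a bivariate normal with correlation 0.5.
- 2.5% each: 4.5% (at most 2 × 2.5% = 5.0%).
- 1.7% each: 3.1% (at most 2 × 1.7% = 3.4%).

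**4. If OM-TM is added as a third comparison.** By simulation, treating all three differences as lying at the margin:
- 2.5% each: about 6.6% (at most 7.5%).
- 1.7% each: about 4.6% (at most 5.1%).

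These are ceilings. OM-SM is the sum of the other two differences, so with one common margin the three cannot all lie on it at once, and the attainable error is lower.

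**5. Power for recurrence.** Power = Φ(δ/SE − z), with SE = √(2 × 0.04 × 0.96/n).
- 170 per arm: δ/SE = 2.823, giving 75.9% at 1.7% and 80.6% at 2.5%.
- 200 per arm: δ/SE = 3.062, giving 82.7% at 1.7% and 86.5% at 2.5%.
- 160 per arm (200 less the stated 20% withdrawal): 73.2% at 1.7% and 78.2% at 2.5%.

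No such figure can be given for AVVQ, because the protocol gives no standard deviation.

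**6. Superiority.** Three unadjusted pairwise tests at two-sided 0.05 give a family-wise error of about 12% (12.2% by simulation), if that is how the comparisons are run.

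**The case against.** The strongest reply is that the two levels belong to different endpoints. The 1.7% is set for recurrence and the 95% CI for AVVQ, so the AVVQ rule does not directly overturn a level set for recurrence. That is correct. It does not remove the inconsistency: the 1.7% is then used nowhere in the analysis, and the endpoint it was meant for has no non-inferiority criterion.

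A reader might also infer that a planned multiplicity control has been lost. The document does not support that, for two reasons. It states no such control, and reading 1.7% as 5%/3 is an inference. And if that reading is right, the planned family-wise level is one-sided 5%, which two tests at 2.5% respect (4.5%, at most 5.0%). The 3.1% comparator is what two tests at 1.7% would give; it is not a stated target.

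A reader might further infer a 12% error for the superiority analyses. The text gives only the 0.05 threshold. It does not say that three unadjusted pairwise tests will be run, and a global three-group test would fit the same sentence. The 12% is therefore conditional.

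Finally, multiplicity detail is often left to an analysis plan that is not shown here. That excuses silence. It does not excuse a sizing level and a decision level that differ within one document, because an analysis plan would have to depart from one of them.

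**Conclusion.** The point holds as a mismatch that should be reconciled. The design level is one-sided 1.7% on recurrence. The only decision level is one-sided 2.5%, on AVVQ, for each of two comparisons. The per-comparison error is about 1.5 times the sizing level, and the chance of at least one false claim is 4.5% against 3.1% with both shorter arms at the margin.

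Whether a family-wise limit is breached depends on a level that the protocol does not state. One-sided 5% is kept for the two named comparisons. It is no longer covered on the usual accounting if all three pairs are tested at 2.5% (about 6.6%, at most 7.5%, both ceilings). One-sided 2.5% is exceeded even with two. The family-wise figures assume equal arms, a two-sided interval and normal approximation.

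**What to change.** **Preferred: carry the sizing level into the analysis.** In Statistical analysis, use two-sided 96.6% CIs for the non-inferiority comparisons. Apply them to the 12-month recurrence difference against the 6-point margin as well as to AVVQ against 2.0 points. Name the comparisons in the family and the family-wise level they share. The cost is intervals about 8% wider. This suits a one-sided 5% family. It does not meet one-sided 2.5%, since two comparisons still give 3.1%.

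**Alternative: one-sided 2.5% with a pre-specified testing order.** Keep the 95% CIs, state the order, and change the 1.7% in Sample size and study duration to match. The later comparison can then be claimed only if the earlier one succeeds. The power must be restated: about 81% at 170 and 86% at 200 evaluable per arm, under 4% recurrence and a 6-point margin. The stated 90% would need 225 per arm, so this option is more than a change of wording.

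**Either way**, give recurrence its own non-inferiority criterion, and if pairwise superiority tests are run, apply the same multiplicity adjustment to them.

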
### Objectives

The primary objective of this study is to determine the recurrence of VVS at 12 month after thermal ablation in patients with different durations of compressure therapy, assessed by duplex ultrasound scanning and clinical physical examination. The secondary objectives are the saphenous vein (GSV) closure rate at 12 month, the closure failure is defined by a segment of the reopen vein ≥5 cm by ultrasound. The VCSS, AVVQ, CIVIQ scores are compared among the three groups at baseline, 1, 3, 6, and 12 month, as well as the pain scores [using the Visual Analog Scale (VAS)] at baseline, 24 h, and 1 month after surgery. Postoperative complications are recorded in three groups, and the compliance of compressure therapy is investigated.

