### Primary outcome

The primary outcome is the recurrence of target VVs at 12 months (21, 22). New recurrence is defined as the postoperative appearance of VVs that did not exist in the VV area in the lower limbs before surgery; primary recurrence is defined as the reappearance of VVs that existed in the VV area before surgery during follow-up. Both types of recurrence are defined as postoperative recurrence.

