### Follow-up

The researcher will assist each patient in outpatient follow-up and data collection at 1, 3, 6, and 12 months (Figure 1). For patients who cannot visit the outpatient clinic for follow-up, follow-up will be completed by video telephone and social media software, and schedule a specific time for the ultrasound examination.

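### Recurrence is defined and sized as a 12-month proportion but analysed only by Kaplan-Meier and Cox, although it is detected only at scheduled examinations

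*Protocol article*

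**What the plan says.** **Endpoint.** The Primary outcome section states: "The primary outcome is the recurrence of target VVs at 12 months". The Objectives section sets the same time point, to "determine the recurrence of VVS at 12 month after thermal ablation", and says how it is found: "assessed by duplex ultrasound scanning and clinical physical examination".

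**Definition.** The Primary outcome section also uses open-ended wording: "primary recurrence is defined as the reappearance of VVs that existed in the VV area before surgery during follow-up".

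**Visits.** The Follow-up section provides for "outpatient follow-up and data collection at 1, 3, 6, and 12 months". For patients who cannot come to clinic, staff are to "schedule a specific time for the ultrasound examination", and no window is given. No visit falls between months 6 and 12.

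**Sizing.** The Sample size and study duration section assumes 4% recurrence at 12 months in the one-month group, a non-inferiority threshold of 6 percentage points (written with a minus sign), 90% power, one-sided 1.7% significance and 20% withdrawal. It arrives at 170 per group, raised to 200.

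**Analysis.** The only method named for recurrence is: "Recurrence rates will be compared using Kaplan-Meier survival analysis and Cox proportional hazards models". The section gives a non-inferiority rule for the AVVQ score, but no rule for recurrence and no way of dating a recurrence.

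**The concern.** Two things do not fit together.

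1. **The estimand.** The endpoint, objective and sample size all concern the proportion with recurrence at 12 months, and the margin is an absolute difference in that proportion. Cox regression gives a ratio of hazards. A 6-point margin cannot be applied to it without a conversion, and none is given.

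2. **The data.** Kaplan-Meier and Cox, as ordinarily run, need a date for each event. Here a recurrence is known only to have begun between two examinations, and after month 6 that interval is six months wide. If the examination date stands in for the event date, recurrence-free patients leave the risk set on the day they attend. Recurrences found in later attenders are then divided by a shrinking denominator.

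At stake is whether the primary result answers the question the trial was sized for. With about 4% recurrence and a 6-point margin, a few percentage points of distortion in the curve matters.

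**Working it through.** **The plan's own figure.** Inputs from the Sample size section: p = 0.04 in both arms, margin 0.06, one-sided 0.017, power 0.90. For a difference in proportions, n per arm = (2.12 + 1.28)² × 2 × 0.04 × 0.96 / 0.06², which is 247 with unrounded quantiles (741 in total). The stated 511 (170 per group) is not reproduced. That is a separate matter. What counts here is that the inputs are those of a risk difference.

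**Step 1: the two scales differ.** Under proportional hazards, 10% against 4% is a hazard ratio of ln(0.90)/ln(0.96) = 2.58.
- Risk difference, 200 per arm: SE = √(2 × 0.04 × 0.96/200) = 0.0196. Power = Φ(0.06/0.0196 − 2.12) = 83%.
- Hazard ratio, 400 × 0.04 = 16 events: SE of the log hazard ratio ≈ 2/√16 = 0.5. Power = Φ(0.948/0.5 − 2.12) = 41%.
- After 20% withdrawal (160 per arm, 12.8 events): 73% and 34%.

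The same data, with a margin equivalent at 4%, support quite different conclusions on the two scales.

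**Step 2: the curve if actual examination dates are used.** Assumptions: one assessment, 4% true recurrence, attendance spread evenly over 365 ± w days, recurrence independent of attendance day. The protocol gives no window, so w is assumed. With F(t) the fraction attended by day t, the Kaplan-Meier recurrence is about 1 − exp{−p × [−ln(1 − F(t))]}.

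| Spread | Day | F | Kaplan-Meier recurrence |
|---|---|---|---|
| ±30 | 365 | 0.50 | 1 − exp(−0.04 × 0.693) = 2.7% |
| ±30 | 380 | 0.75 | 1 − exp(−0.04 × 1.386) = 5.4% |
| ±30 | 389 | 0.90 | 1 − exp(−0.04 × 2.303) = 8.8% |

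Simulation with 200 per arm gives the same values. A tighter window does not remove the effect: simulated values for ±14 days are about 2.8% at day 365 and 8% to 9% at day 376.

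If half of the recurrences are found at earlier visits, 2% are removed first and the rest follow the same pattern: 1 − 0.98 × exp{−(0.02/0.98) × [−ln(1 − F)]}. This gives about 3.4% at day 365 and 6.5% at day 389; simulation agrees to within 0.1 point.

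**Step 3: the hazard ratio under a timing difference.** Equal 4% recurrence in both arms, ±30-day spread, one arm attending later (assumed). The hazard ratio is simulated with 2,000 per arm to reduce noise.
- 10 days later, single assessment: about 0.5. At 200 per arm a nominal 5% test rejects in about a quarter of trials.
- 10 days later, half found earlier: about 0.7, with rejection of roughly 7% to 10%.
- 5 days later, single assessment: about 0.7.
- No timing difference: 1.0, with rejection near 5%.

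**Step 4: nominal visit times.** With events and censoring coded to month 12, or to months 1, 3, 6 and 12, Kaplan-Meier returns 4.0% in both arms. Log-rank type I error is 4.9% and 5.6% respectively (1,000 runs). The distortion disappears.

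**The case against.** The strongest defence has four parts.

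- **Earlier assessments may exist.** The definition counts reappearance during follow-up, visits occur at months 1, 3 and 6, physical examination is possible at any of them, and the schedule figure is not available here. A reader might infer that month 12 is the only assessment. The text ties recurrence explicitly to that month alone, but this does not show that nothing earlier is planned. This part stands.
- **The dating rule is not stated.** A reader might infer that the Kaplan-Meier and Cox results are bound to reflect attendance rather than recurrence. That follows only if actual dates are used, and a full protocol or analysis plan may say otherwise. With nominal times, Kaplan-Meier read at month 12 is the cumulative proportion. This part also stands.
- **Differential timing is an assumption.** All arms share one schedule, and the Data collection section has every participant reminded before each visit. Patients and physicians are unblinded, so a difference is possible, but nothing in the document shows one. The hazard ratio of about 0.5 is a what-if, not a forecast.
- **Censoring accommodates withdrawals.** This is a real convenience, but it assumes that patients who withdraw have the same recurrence risk as those who stay.

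None of this removes the mismatch between a risk-difference design and the named analysis, or the fact that onset is interval-censored.

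**Conclusion.** The point holds as a mismatch in the analysis of the primary outcome. The endpoint and sizing concern a 12-month proportion with a 6-point margin. The only stated analysis is time-to-event, and its hazard ratio does not estimate that difference.

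The size of any distortion is conditional. It needs actual examination dates as event and censoring times. On that footing, with 4% recurrence and an assumed ±30-day spread, the curve runs from about 2.7% at day 365 to 8.8% at day 389 with one assessment, and from about 3.4% to 6.5% if half of recurrences are found earlier. Bias in the between-arm comparison needs a timing difference between arms as well. The document does not support saying that the time-to-event estimate is wrong in every case.

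The change is still worth making before any unblinded analysis: it concerns the primary outcome, the better method is specific, and it costs little.

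**What to change.** In the Statistical analysis section:

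1. Make recurrence status by the 12-month visit, within a fixed window, the primary analysis. Report the proportion per arm and the between-arm risk difference, with its confidence interval set against the 6-point margin.
2. State the method for missing 12-month outcomes, with a sensitivity analysis. At the anticipated 20% withdrawal, 200 × 0.20 = 40 patients per arm could lack an outcome, against 200 × 0.04 = 8 expected recurrences, so this choice can affect the result.
3. State at which visits recurrence is assessed.
4. Keep time-to-event only as secondary, with events and censoring assigned to the nominal visit and a discrete-time or interval-censored model.

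**Cost.** Wording and a visit-window rule, with no new visits or patients. The trial gives up a headline survival curve, and withdrawals need explicit missing-outcome handling instead of censoring.

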**Methods:**

This will be a prospective, multicenter, randomized, parallel-group trial. This study will include 600 patients with great saphenous vein insufficiency (C2–C6) treated with endovenous radiofrequency or laser ablation at 7 high-volume centers. The participants will be randomly assigned to the following groups at a 1:1:1 ratio: the one-month (OM) group, which will wear class II compression stockings (23–32 mmHg) for 1 month after surgery; the three-month (TM) group, which will wear compression stockings for 3 months; and the six-month (SM) group, which will wear compression stockings for 6 months. All the groups will wear the same compression stockings and follow the same instructions for wearing the stockings. The primary outcome is the recurrence of VVs at 12 months; the secondary outcomes include the closure rate of the great saphenous vein, disease-specific quality of life assessed by the Aberdeen Varicose Vein Questionnaire (AVVQ), the Chronic Lower Limb Venous Insufficiency Questionnaire (CIVIQ) score, the Venous Clinical Severity Score (VCSS), the incidence of postoperative complications (pain, ecchymosis, paresthesia, deep vein thrombosis, etc.), and patient compliance. The follow-up times are 1, 3, 6, and 12 months after surgery.

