### Randomization and blinding

Eligible, consenting patients will be randomized at a 1:1:1 ratio to one of the following groups: the one-month group (OM group, elastic stockings for 1 month), three-month group (TM group, elastic stockings for 3 months), and six-month group (SM group, elastic stockings for 6 months) using a central, computer-generated, stratified block randomization sequence via a secure randomization-generated web-based system. Patients and physicians cannot be blinded owing to the nature of the intervention (duration visible to the patients). The outcome assessors (Duplex ultrasound technicians, QoL questionnaire administrators) and statisticians will be blinded to group allocation.

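### Randomisation is stratified by unnamed factors, yet the primary recurrence comparison states no strata and the complication tests are unstratified; the cost is small and conservative

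*Protocol article*

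**What the plan says.** Under Randomization and blinding, the protocol article allocates patients 1:1:1 with a "central, computer-generated, stratified block randomization sequence via a secure randomization-generated web-based system". It does not say what the strata are.

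The Statistical analysis section treats the types of outcome differently:

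- Continuous outcomes: "linear mixed models (LMMs) adjusted for baseline values, center, CEAP class, and time".
- Recurrence: "Recurrence rates will be compared using Kaplan-Meier survival analysis and Cox proportional hazards models". No strata or covariates are given. This is the primary endpoint, since the Primary outcome section states: "The primary outcome is the recurrence of target VVs at 12 months".
- Complications: "Complications will be compared using chi-square tests or Fisher’s exact tests". No stratified version is mentioned.

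Two further facts bear on any remedy. According to the abstract, patients are "treated with endovenous radiofrequency or laser ablation at 7 high-volume centers", and the inclusion criteria admit CEAP classes C2 to C6, which is five classes. CEAP class is also named as a planned subgroup factor.

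**The concern.** Stratified allocation balances the arms on the stratification factors. If those factors predict the outcome, the treatment difference varies less from trial to trial than a formula for simple randomisation assumes. An analysis that leaves the factors out still charges that between-stratum variation to error, so its interval is wider than the design warrants. The usual principle is to analyse by the factors used to randomise.

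Here one paragraph spells out adjustment for the secondary continuous outcomes and none for the primary. Applied literally, it gives adjusted secondary analyses beside an unadjusted primary one. Recurrence is sized as a non-inferiority comparison with a 6-point margin, and a wider interval makes non-inferiority harder to show. The choice also needs fixing in advance, because recurrences will be few and the obvious repair, reusing the mixed-model covariates, would overload the model.

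**Working it through.** **Inputs from the protocol article.** 600 patients, 200 per arm; recurrence set at 4%, range 3–5%; margin 6 points; one-sided level 1.7%; 20% withdrawal (Sample size and study duration). 7 centers (abstract). CEAP C2–C6 (Inclusion criteria).

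**Inputs that are assumptions.** The article names no strata and gives no effect of center or CEAP class on recurrence. The checks below suppose that center and a two-level CEAP grouping are the strata, and they vary the strength of the effects.

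**1. Expected events.** 600 × 0.03 = 18; 600 × 0.04 = 24; 600 × 0.05 = 30. For one pairwise comparison, 400 × 0.04 = 16. Spread over 7 × 2 = 14 strata, that is 16/14 ≈ 1.1 events per stratum.

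**2. Simple calculation, CEAP alone.** Suppose 80% of patients are C2–3 with 2.5% recurrence and 20% are C4–6 with 10%.

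- Mean risk: 0.8 × 0.025 + 0.2 × 0.10 = 0.04.
- Between-stratum variance: 0.8 × 0.015² + 0.2 × 0.06² = 0.00018 + 0.00072 = 0.0009.
- Total variance: 0.04 × 0.96 = 0.0384.
- Share explained: 0.0009/0.0384 = 2.3%.
- True SE over unstratified SE: √(1 − 0.0234) = 0.988, so the unstratified SE is about 1.2% too large.

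**3. Simulation with center and CEAP effects.** One-month against six-month arm, about 200 per arm, mean recurrence 4%, 7 centers × 2 CEAP groups, 25% of patients in the higher group, permuted blocks of 6, 6,000 to 15,000 runs. The unstratified SE of the risk difference was compared with its empirical SD, under no true treatment difference.

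| Center SD (logit) | CEAP odds ratio | Unstratified SE / empirical SD | Rejection at nominal two-sided 5% |
|---|---|---|---|
| 0 | 1 | 0.99–1.00 | 4.8–5.1% |
| 0.5 | 2 | 1.00 | 4.6–5.0% |
| 1 | 3–5 | 1.03–1.04 | 3.7–4.2% |

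With center SD 1 and odds ratio 3, one set of runs gave a model SE of 0.01938 against an empirical SD of 0.01881, a ratio of 1.03. In that set the Mantel-Haenszel estimate had an empirical SD of 0.01877, nearly the same as the unstratified estimate. The randomisation has already delivered the balance; what is off is the reported standard error.

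**4. Effect on power.** A separate simulation used the 80/20 scenario, blocks of 4, the 6-point margin, one-sided 1.7% and 6,000 runs.

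| Scenario | Unstratified | Mantel-Haenszel |
|---|---|---|
| 200 per arm, CEAP only | 82.5% | 82.8% |
| 200 per arm, plus center SD 0.5 (log scale) | 83.7% | 84.6% |
| 160 per arm | 73.6% | 74.8% |

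The difference is about 1 point at most.

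**5. Attenuation of the hazard ratio.** Take the strata of step 2 and a within-stratum hazard ratio of 2.00. Marginal 12-month survival is 0.8 × 0.975 + 0.2 × 0.90 = 0.96 in one arm and 0.8 × 0.975² + 0.2 × 0.90² = 0.9225 in the other. The ratio of cumulative hazards is ln(0.9225)/ln(0.96) ≈ 1.98. The pull toward 1 is trivial.

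**6. Ordinary covariates in the Cox model.** Center takes 6 parameters, CEAP class 4 and arm 2, which makes 12. With 24 events that is 2 events per parameter.

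**7. Variance of the stratified estimate.** With strata this sparse, a plain within-stratum binomial variance came out about 5–8% too small in simulation. A Mantel-Haenszel risk difference therefore needs a variance suited to sparse data.

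**The case against.** The strongest reply is that the article is silent rather than wrong. It never calls the Cox model unadjusted, a Cox model readily takes strata or covariates, and a condensed article may leave that detail to a fuller document. Chi-square and Fisher tests are ordinary choices for 30-day complications. Covariates chosen for quality-of-life scores need not predict recurrence. The numerical effect is slight, and sparse strata bring their own difficulty.

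Much of this stands, and it rules out several stronger readings that a reader might infer:

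- *That center and CEAP class are the randomisation strata.* They appear only as mixed-model covariates. The randomisation factors are not named.
- *That the primary analysis has been fixed as unadjusted.* The text states no adjustment but does not exclude it.
- *That the error rate is compromised.* Any mismatch widens intervals, and simulated rejection was at or below nominal apart from simulation error.
- *That the hazard ratio is materially biased toward 1.* At about 4% recurrence it is not.

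What survives is the uneven specification. The same paragraph chooses to state adjustment for the secondary continuous outcomes, states none for the primary, and names complication tests that are unstratified as written. That is a stated method which can be improved at almost no cost.

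**Conclusion.** The point holds as a minor mismatch between design and analysis. Allocation is stratified, the recurrence comparison states no strata, and the complication tests have none. If the strata are prognostic, unstratified recurrence intervals would be about 0–4% too wide, with power lower by about 1 point at most and no inflation of type I error. These sizes rest on assumed strata, CEAP shares, center and CEAP effects and block sizes, since the article gives none of them. If the actual factors do not predict recurrence, the loss is essentially nil. The rejection rates were simulated under no treatment difference, not at the non-inferiority margin; an over-wide interval errs in the same direction there.

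**What to change.** 1. Name the stratification factors under Randomization and blinding.
2. State that recurrence is analysed stratified by those factors. A stratified log-rank test or Cox model keeps the planned time-to-event approach. A Mantel-Haenszel risk difference with a sparse-data variance such as Sato's is the alternative, and it is on the scale of the 6-point margin.
3. Compare complications with the Cochran-Mantel-Haenszel test over the same strata, in exact form where counts are small.
4. Fix a rule for pooling sparse strata before unblinding, for example C2–3 against C4–6 if CEAP class is a factor.
5. Do not enter center and CEAP class as 10 ordinary covariates in a Cox model with about 24 expected events.

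The cost is a few sentences of text. CEAP class is already recorded at baseline, and the allocation system must already hold the stratum of each patient. The downside is that a pooling rule has to be agreed, for a modest gain in precision.
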